# 1 ABBREVIATIONS

AE Adverse Events

App Application

BTA British Tinnitus Association (now known as Tinnitus UK)

CBT Cognitive Behavioural Therapy

CI Chief Investigator

TSC Trial Steering Committee

e-Consent Electronic consent

eTMF Electronic Trial Master File

EDC Electronic Data Capture

EQ-5D-5L EuroQol Questionnaire

GCP Good Clinical Practice

GDPR General Data Protection Regulation

GP General Practitioner

HRA Health Research Authority

HUI Health Utilities Index

ICF Informed Consent Form

ICH International Conference on Harmonisation

ITT Intention To Treat

NICE National Institute for Health and Care Excellence

PIS Patient Information Sheet

PPS Per Protocol Analysis Set

REC Research Ethics Committee

RCT Randomised Clinical Trial

RN Research Nurse

SAE Serious Adverse Event

SAP Statistical Analysis Plan

SUS System Usability Scale

TFI Tinnitus Functional Index

THI Tinnitus Handicap Inventory

TMG Trial Management Group

TRT Tinnitus Retraining Therapy

UKRI United Kingdom Research and Innovation

KEYWORDS: tinnitus, digital therapeutics, cognitive behavioural therapy (CBT), health economics.

# 2 STUDY SYNOPSIS

| Title | Digital thErapy For Improved tiNnitus carE |
| --- | --- |
| Short title | DEFINE |
| Chief Investigator | [name] |
| Background | Tinnitus is a common condition, affecting approximately 15% of UK adults. It is usually perceived as a buzzing or ringing in the ears, without a stimulus in the outside world. There is currently no cure, but cognitive behavioural therapy (CBT) has been shown to be effective in reducing self reported distress and illness severity. Unfortunately, access to CBT is limited, with significant healthcare costs associated with provision and additional costs to people with tinnitus including time away from work, travel and lost productivity. |
| Primary objective | To assess whether Oto’s digital tinnitus programme is no worse at reducing self-reported tinnitus severity as therapist-delivered CBT |
| Secondary objectives | - Assess whether Oto’s digital tinnitus programme is superior to therapist-delivered CBT in reducing self-reported tinnitus severity - Assess the self-reported impact of Oto’s digital tinnitus programme on aspects of participants tinnitus experience - Assess the impact on overall health-related quality of life of Oto’s digital programme and human delivered CBT - Assess the usability of the Oto digital programme - Explore participants views of the impact and usability of Oto’s digital programme - Understand the health economic consequences of using a digital therapeutic for tinnitus - Assess the number of adverse events between the groups - Assess intervention Adherence |
| Study design | An open-label, non-inferiority, prospective, parallel design, randomised-controlled study assessing the Oto smartphone tinnitus management programme versus therapist delivered CBT in achieving improvement in self-reported tinnitus severity in adults. |
| Phase | III |
| Setting | Fully decentralised study with participants recruited remotely. Interventions and assessments delivered remotely via the Oto health smartphone app, video calls and the Lindus Health platform. |
| Recruitment Strategy | Patients will be recruited centrally by the Lindus Health research team, with Lindus Health acting as a research site. Patients will be identified via primary care, advertising on social media and to patient communities, in addition to healthcare professionals directing potential participants to the trial website. Patients can receive £40 for taking part in the trial. |
| Primary Outcome | Total TFI score (Score of 0-250 with high score indicating worse outcome) 6 months from starting therapy |
| Secondary Outcomes | 1) Total TFI and TFI subscale scores at 1, 3 and 12 months  2) Participant health-related quality of life measured using the EuroQol EQ-5D-5L and the Health Utilities Index Mark 3 (HUI3) responses and summary scores at 3, 6 and 12 months follow-up from starting therapy  3) Adverse events from randomisation to 3 months  4) System Usability Scale scores at 3 months  5) Qualitative feedback from focus groups and semi structured interviews at 3, 6 and 12 months  6) Cost-utility analysis synthesising costs and QALYs over trial period  7) Assess intervention adherence at 3 and 6 months |
| Number of participants | 196 participants, randomised in a 1:1 ratio |
| Eligibility criteria | Inclusion Criteria   1. Aged 18 years or over 2. Experienced tinnitus symptoms for at least 3 months and self-assessed as having a significant impact on quality of life. 3. Have access to a smartphone 4. Able and willing to give consent for the study prior to participation 5. Able to speak and read English to a sufficient level.   Exclusion Criteria   1. Tinnitus with potential “red flag” symptoms i.e. unilateral or pulsatile tinnitus (assessed via a red flag checklist during the screening call) 2. Significant mental health problems e.g. history of suicidal ideation or requirement for psychiatric/psychological support beyond Primary Care level 3. Have required hospitalisation for depression or taking antipsychotic drug 4. Currently taking part in another clinical trial for hearing/tinnitus 5. Awaiting surgical intervention for hearing/tinnitus 6. Previously undergone tinnitus therapy of any type e.g. CBT or TRT 7. Pregnant and breastfeeding women   Additional Note: Patients with hearing aids are eligible to participate in the study |
| Intervention | The Oto digital programme for tinnitus. This involves direct access to a digital multi-modal therapy package incorporating CBT, physical therapy, mindfulness and relaxation therapy. |
| Comparator | Current standard of care (1-1 therapist-delivered CBT). |
| Duration of study | 18 months |
| Randomisation / Blinding | Randomised 1:1 by computer algorithm and stratified by age, sex and level of hearing loss. Unblinded. |
| Statistical analysis | Non-inferiority |
| Intervention Adherence | Number of participants in each group completing therapy programme by 3 months |

# 3 BACKGROUND and RATIONALE

3.1 Background

Tinnitus is the perception of sound in the absence of an external stimulus. Tinnitus is very common with approximately 15.3% of the UK population experiencing prolonged tinnitus with 5.4% considering this bothersome^1^. Prevalence varies with age, with approximately 10% of younger adults, 14% of middle aged adults and 24% of older adults experiencing tinnitus^2^.

Treatment options for people with tinnitus are currently suboptimal. The approach with the strongest evidence base is Cognitive Behavioural Therapy (CBT), with guided self-directed CBT showing the largest effect size and having the highest likelihood of being ranked first in improving tinnitus health-related quality of life (75%), depression (83%), and anxiety (87%)^3^. Current NHS provision as delivered by Ear, Nose and Throat Surgeons, Audiologist and Hearing Therapists, focuses on ensuring there are no concerning features, such may indicate cerebellopontine angle pathology or systemic health problems. Once these are ruled out, patients may be offered referral for tinnitus therapy. Provision of this therapy, both in terms of access and method of delivery, is inconsistent. Current NICE guidance advocates a combination of reassurance, mitigation of any underlying cause if possible, optional hearing aiding if concomitant hearing loss is present, self-care advice and consideration of referral for psychological therapy^4^.

Current NHS tinnitus therapy provision is typically based on the principles outlined in Tinnitus Retraining Therapy (TRT), though some elements of Cognitive Behavioural Therapy (CBT) and relaxation may also be incorporated. Provision outside the NHS is more varied, usually featuring longer term support and contact and a wider range of therapeutic techniques. This provision is typically on a one-to-one basis and lasts between one and ten sessions. However, many people with tinnitus do not access such support and an opportunity exists to expand provision to this underserved group as well as supplementing and optimising current provision for those able to access therapeutic support.

The proliferation of smartphone technology has led to the development of a number of app-delivered therapies for a variety of health conditions, partially stimulated by the COVID-19 pandemic^5^. These have been deployed most extensively for mental health indications with both primary research and evidence synthesis to support their use^6^. At present a number of such apps are available for tinnitus, though they predominantly rely on sound therapy (masking)^7,19^.

Oto is a novel multimodal smartphone app-delivered approach to tinnitus. It combines patient education, CBT, relaxation, mindfulness and sound therapy in a customisable package. The self-paced and self-administered delivery method also allows patients to avoid taking time off work and eliminates travel time to a hospital. In contrast to traditional therapy, the app removes limits on the number of individuals that can be served at the same time, and has the potential to significantly advance capacity at a time when waiting lists are under severe pressure.

3.2 Rationale

Tinnitus presents a large burden on society: with 1m+ GP appointments for tinnitus, the NHS spends c.£750m annually, and with loss of productivity among other costs, tinnitus is responsible for an annual loss to the economy of £2.7b in the UK^16^.

The main aim of this study is to assess whether Oto’s digital therapeutic is no less effective than current standard of care (human delivered CBT) as defined by change in self-reported tinnitus severity, as measured by the Tinnitus Functional Index at six months from starting therapy. A cost-utility analysis will be undertaken to evaluate the potential of the Oto app to represent value for money for the NHS and society more widely.

# 4 OBJECTIVES AND OUTCOME MEASURES

4.1 Randomised Controlled Trial

Primary Objective

| **Objective** | **Outcome Measure** | **Timepoint(s) of evaluation** |
| --- | --- | --- |
| Assess whether Oto’s digital tinnitus programme is as effective at reducing self-reported tinnitus severity as therapist- delivered CBT | Total TFI score | Primary outcome is total TFI score at 6 months  TFI evaluated at:  Baseline, 1, 3, 6 and 12 months |

Secondary Objectives

| Objective | Outcome Measure | Timepoint(s) of evaluation |
| --- | --- | --- |
| Assess whether Oto’s digital tinnitus programme is superior to therapist-delivered CBT in reducing self-reported tinnitus severity | Total TFI score | Total TFI score at 6 months |
| Assess the self-reported impact of Oto’s digital tinnitus programme on aspects of participants tinnitus experience | 8 Tinnitus Functional Index subscales (Intrusive, Sense of Control, Cognitive, Sleep, Auditory, Relaxation, Quality of Life and Emotional). | Baseline, 1, 3, 6 and 12 months |
| Assess the impact on overall health-related quality of life of Oto’s digital programme and therapist delivered tinnitus therapy | EuroQol EQ-5D-5L and Health Utilities Index Mark 3 (HUI3) | Baseline, 3, 6 and 12 months |
| Assess the usability of the Oto digital programme | System Usability Scale | 3 months |
| Explore participants views of the impact and usability of the two interventions | Thematic analysis of focus groups and semi structured interviews | 3, 6 and 12 months |
| Understand the health economics of the two for tinnitus | Cost-utility analysis | Over trial period covering from baseline to 12 months |
| Assess the number of adverse events between the groups | eCRF | Randomisation to 3 months |
| Assess intervention Adherence | Number of participants completing the intervention | Number of participants starting the intervention at baseline compared to those completing the intervention at 3 and 6 months |

# 5 STUDY DESIGN

5.1 Study Type

Prospective, open-label, randomised controlled, parallel design with an active control.

5.2 Duration

Participants will be assigned to the intervention or standard usual care for 12 months, with an additional 1-week onboarding prior to this.

# 6 PARTICIPANT IDENTIFICATION

## 6.1 Study population

Adults with tinnitus that has persisted for at least 3 months and is self-assessed as impacting quality of life. Participants must not have previously undergone tinnitus therapy (TRT or CBT by any delivery method).

Participants may be identified by:

- searches of primary care electronic health records
- potential participants may be directed to the study website by any clinician seeing them for the condition
- participants can self present using the website in response to social media or patient community advertising.

6.1.1 Inclusion Criteria

Participants must meet all the following criteria:

Inclusion Criteria

1. Aged 18 years or over
2. Experienced Tinnitus symptoms for >= 3 months and self-assessed as impacting quality of life
3. Have access to a smartphone
4. Able and willing to give consent for the study prior to participation
5. Able to speak and read English to a sufficient level

6.1.2 Exclusion criteria

Participants meeting any of the following criteria are not eligible for inclusion in the study:

1. Tinnitus with potential “red flag” symptoms (e.g., unilateral or pulsatile tinnitus)
2. Significant mental health problems e.g. history of suicidal ideation or requirement for psychiatric/psychological support beyond Primary Care level
3. Have required hospitalisation for depression or taking antipsychotic drug
4. Currently taking part in another clinical trial for hearing/tinnitus
5. Awaiting surgical intervention for hearing/tinnitus
6. Previously undergone tinnitus therapy of any type e.g. CBT or TRT
7. Pregnant or breastfeeding women

The rationale for excluding “Pregnant and breastfeeding women” is that this population was not able to be included in the trial insurance coverage.

## 6.2 Recruitment of Participants

Potential participants will be identified via several different mechanisms:

1. Clinicians working at GP practices (Participant Identification Centres - PICs) within the Lindus Health Primary Care Network (this covers GP groups, networks or single practices across the UK) will be informed of the study and will describe the study to patients presenting tinnitus symptoms of at least 3 months. If the patient is interested in knowing more about the study they will be directed to the trial website where more information about the trial will be displayed and have the choice to sign up to receive the patient information sheet and a video explaining the trial.
2. The electronic medical records of patients at participating primary care practices (Participant Identification Centres - PICs) within the Lindus Health Primary Care Network. GP practices will be provided with a search for their registers to identify potential participants, who will be invited to take part in the trial via a text message directing them to the trial webpage where they will be able to receive more information about the trial and have the choice to sign up to receive the patient information sheet and a video explaining the trial.
3. Social media advertising on Facebook and other platforms will be used to highlight the trial to individuals with tinnitus. Adverts will make clear that the study does not replace the need to seek medical advice. Adverts will direct potential participants to the study website, where more information about the trial will be displayed and have the choice to sign up to receive the patient information sheet and a video explaining the trial.

All participants will receive up to £40 for taking part in the trial.

# 7 TRIAL PROCEDURES

Trial procedures are detailed in the Trial Flow Chart (Appendix 1). The study will be conducted in keeping with the Good Clinical Practice guidelines and regulations.

## 7.1 Digital Applications

For the duration of the trial participants will be asked to record their responses to questionnaires directly into the Lindus Health Electronic Data Capture (EDC) platform, via a participant survey link, which will be emailed and/or texted to them. The participants in the smartphone delivered CBT arm will also use the Oto tinnitus app. Certain fields may require duplicate data entry between the two digital systems, but it is essential that data on the Lindus Health platform is completed fully.

The Lindus Health team will have access to the EDC data and will review this on a daily basis (excluding weekends). Missing data will trigger an alert message to the participant via text/email. If no response is entered, a daily reminder will be triggered for 3 days, after which point the Lindus Health team will contact the participant to assess if they wish to withdraw from the study. If a participant wishes to withdraw then they will be advised to arrange an appointment with their GP or healthcare provider to discuss other treatment options (i.e. return to standard care), and a reason for withdrawal will be documented. Free access to the app will continue for participants in the Oto arm, or be offered free for 12 months from completion of the study for participants in the control group.

## 7.2 Pre-screening

The potential participant will be directed to the trial web page, where they will be informed about the trial via the study website. If interested in taking part, they will complete an online pre-screening form to assess their eligibility for the trial. If potentially eligible and once they submit the form, the Patient Information Sheet (PIS) and Informed Consent Form (ICF) will be emailed directly to the participant, as well as a video explaining the trial, and they will be asked to book a telephone/video call with a member of the central trial team.

## 7.3 Informed consent

Prior to consent, the patient will have received via email the PIS, ICF and video describing the trial. They will have had the opportunity to read through the details relating to the exact nature of the trial, the known side-effects and any risks involved in taking part. It will be clearly stated that the participant is free to withdraw from the study at any time for any reason without prejudice to future care, without affecting their legal rights, and with no obligation to give the reason for withdrawal. It will be confirmed that potential participants have reviewed the PIS.

Participants will be asked to provide informed consent only after a discussion with a suitably qualified and delegated member of the central trial team and prior to randomisation. Adequate time will be given to the participant to consider the information and to ask any questions about the trial before deciding whether to participate. If the participant is willing, informed consent will be obtained. The participant will provide their electronic signature at the end of the e-consent form and the central trial team member will countersign the form. A copy of the fully executed ICF will be sent to the participant by email and an electronic copy retained by Lindus Health in a secure area with restricted access. The participant’s GP will be informed of their involvement in the trial.

Identifiable participant details (confidential details, including name and date of birth) will be held in a database separated from the research database after receiving participants consent. The research database will never hold personal identifiable information. Automatic reminders will be sent to participants by doing a one-time recall of the identifiable information by matching the unique study ID.

## 7.4 Screening and Eligibility Confirmation

Screening will be conducted remotely by a member of the central trial team, during the same telephone/video call where informed consent is obtained. A member of the central trial team will use the medical history obtained from the participant to confirm that the participant meets the inclusion and exclusion criteria. A record of screen failures that do not meet the inclusion/exclusion criteria will be retained.

Given the low risk of intervention, participant eligibility will be assessed by a member of the central trial team who will assess this against the self-reported medical criteria to determine suitability for the study.

## 7.5 Hearing screening

When the consent form is sent out participants will be asked in advance to have headphones available at the time of their screening and consent phone call. For participants who consent to trial involvement they will be directed to download a smartphone application to screen their hearing for the sole purpose of stratification at randomisation. Participants will be asked if they have an ios or Android-based smartphone. Those with an ios-based device will be asked to download the ‘Easy Hearing Test’ application (produced by Hiroaki Ito) . Those with an Android-based phone will be asked to download the ‘Hearing test’ app (produced by e-audiologica).

Both applications are free to the user and do not require the user to register or share personal identifiable data.

Participants will be given instructions on use of the apps, and allowed to complete the hearing test for both ears, which typically takes around 5 minutes. The participant will then share the hearing test audiogram result with the member of the trial team leading the video call, this image will also be screen captured and stored in the trial database. The trial team will store the data associated with the participants trial ID and record the mean pure tone threshold at 0.5, 1, 2 and 4kHz. All participants will be encouraged to seek formal audiometric testing (see below) rather than to rely on the screening hearing test as it will be made clear that these results are not diagnostic. We have validated these applications ourselves in the home environment, and demonstrated good correlation with hospital pure tone audiogram results (unpublished data).

## 7.6 Randomisation

Following confirmation of eligibility, the participant will be randomised using a secure, fully validated and compliant web-based randomisation system called Sealed Envelope.

Participants will be randomised into one of the two groups at a ratio of 1:1, stratified by

1. Age (<40, >=41-<=60, >61)
2. Sex (Male, Female)
3. Pure tone average threshold based on home hearing test (mean threshold at 0.5, 1, 2, 4 kHz (‘None’ <=15dB, ‘Slight’ 16-25dB, ‘Mild’ 26-40dB, ‘Moderate’ 41-55dB, ‘Moderately severe’ 56-70dB, ‘Severe’ 71-90dB, ‘Profond‘ 91dB+)

1. Control arm: participants will receive one to one therapist-delivered tinnitus therapy from an audiologist/hearing therapist. The specification for the tinnitus therapy to be provided as a control intervention can be found in Appendix 3. This will be delivered remotely, and will consist of a minimum of 1 session, with further sessions at the discretion of the participant and therapist up to a maximum of 6. Therapy will begin within +/- 1 week of randomisation. There will be a panel of therapists selected to deliver the therapy, with all individuals having experience of NHS tinnitus care. The therapy provided will broadly conform to the standard NHS treatment as outlined below.
2. Intervention arm: participants will receive the Oto tinnitus programme (smartphone app delivered CBT). This includes an evaluation of symptoms and tinnitus severity, CBT, mindfulness and other interventions. More details on the Oto app can be found here: <https://www.joinoto.com>

A member of the central trial team will inform the participant during their eligibility call or directly call the participant to inform them of their randomisation allocation, and they will also be sent an email confirmation.

Randomisation represents trial day 1 and outcome assessments will be timed from this point.

## 7.7 Baseline Measurements (Day 1, up to + 7 days)

Once randomisation has been confirmed and prior to starting the intervention, participants will report baseline measurements in their survey which will include but not limited to:

- Complete information on previous treatment for tinnitus and costs already incurred e.g. over the counter supplements, hearing aids
- Complete TFI questionnaire
- Complete EQ-5D-5L and HUI3 questionnaires

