## 7.8 Administration of intervention

Following baseline data collection the participant will be granted access to either the trial intervention or control intervention. Access to the Oto app will be immediate. The first face-to-face CBT appointment will be scheduled within +/- 1 week.

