## 10.1 Description of Statistical Methods

The primary analysis will be conducted on the intention-to-treat (ITT) population. In addition to this, a per-protocol analysis will also be planned as a sensitivity analysis. Compliance will be defined as a minimum of 60 minutes of total use for the intervention group, and one or more sessions for the CBT group. Participants reporting poor compliance will be recorded and these participants will be included in the ITT analysis. Adherence to the smartphone app delivered programme will be monitored through the app with results analysed by intention-to-treat (ITT).

The primary outcome will be reduction in total TFI score at the 6 month point in the ITT population. Non-inferiority will be assessed by constructing a 95% confidence interval around the mean difference in TFI reduction between the groups, and comparing the -upper bound of the confidence interval to the pre-specified non-inferiority margin.

A secondary analysis of the primary outcome will examine significant differences between the control and intervention group’s TFI score at 6 months using a general linear model or a comparable suitable method, using the stratification variables and other potential confounding variables as covariates.

As a sensitivity analysis, the primary outcome will be analysed using the Per-Protocol (PP) population, which consists of participants complying with the treatment regimen. Compliance will be defined as a minimum of 60 minutes of total use for the intervention group, and one or more sessions of CBT for the control group.

Secondary outcomes will be compared between groups and over time with mixed-effects regression models for repeated measures, using the stratification variables and other potential confounding variables as covariates. Logistic models will be used for binary outcomes, and Gaussian models for continuous outcomes. An interim analysis may be conducted once a sufficient number of participants have completed the 6 month milestone. The results of the interim analysis do not influence the continuation of the trial.

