# 22. APPENDIX 1 – TRIAL FLOW-CHART

| **Recruitment**  Primary care, social media, patient communities |
| --- |

↓

| **Prescreening and Registration**  Potential participants directed to LH website. Registered in the LH system. PIS, ICF, video emailed, screening call booked |
| --- |

↓

| **Enrolment**  Potential participants checked against I/E criteria, consent confirmed, randomised to study arm. |
| --- |

↓

| **Sponsor, Participant, GP notified**  Details of randomised participants shared and enrolment confirmed |
| --- |

↓

| **Intervention Arm**  Onboarded to the Oto Tinnitus Programme for 6W | **←** | **Treatment Phase Begins**  Participants enrolled on schedule of assessments and baseline collected | **→** | **Control Arm**  Therapist delivered CBT by a trained specialist |
| --- | --- | --- | --- | --- |

↓

| **Month 1 Follow Up**  Remote contact for outcome measurements |
| --- |

↓

| **Month 3 Follow Up**  Remote contact for outcome measurements |
| --- |

↓

| **Month 6 Follow Up**  Remote contact for outcome measurements |
| --- |

↓

| **Month 12 Follow Up**  Remote contact for outcome measurements |
| --- |

↓

| **End of Trial** |
| --- |

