# 23. APPENDIX 2 - SCHEDULE OF EVENTS TABLE

| **Procedure** | **Pre-screener**  Week -*N* | **Screening**  Week 1, Day 0 | **Randomisation**  Day 0 | **Baseline**  Week 1, Day 1 (+ 7 days) | **Oto App starts for 6wks / consultation for CBT booked**    Day 1 | **Month 1 Follow Up**  Week 4, Day 1 (+/- 7 days) | **Month 3 Follow Up**  Week 12, Day 1 (+/- 14 days) | **Month 6 Follow Up**  Week 24, Day 1 (+/- 14 days) | **Month 12 Follow Up**  Week 52, Day 1 (+/- 28 days) |
| --- | --- | --- | --- | --- | --- | --- | --- | --- | --- |
| Informed Consent | ✓ | ✓ |  |  |  |  |  |  |  |
| Eligibility assessment | ✓ | ✓ |  |  |  |  |  |  |  |
| Medical history | ✓ | ✓ |  |  |  |  |  |  |  |
| Demographics |  | ✓ |  |  |  |  |  |  |  |
| Tinnitus Background Survey |  |  |  | ✓ |  |  |  |  |  |
| Tinnitus Functional Index (TFI) |  |  |  | ✓ |  | ✓ | ✓ | ✓ | ✓ |
| EQ-5D-5L |  |  |  | ✓ |  |  | ✓ | ✓ | ✓ |
| HUI3 |  |  |  | ✓ |  |  | ✓ | ✓ | ✓ |
| Resource Use Questionnaire |  |  |  |  |  | ✓ | ✓ | ✓ | ✓ |
| System Usability Scale |  |  |  |  |  |  | ✓ |  |  |
| AE review |  |  |  | ✓ |  | ✓ | ✓ |  |  |
| Study Experience Questionnaire |  |  |  |  |  |  | ✓ | ✓ | ✓ |
| Adherence Data collected (eCRF) |  |  |  |  |  | ✓ | ✓ | ✓ | ✓ |

#

#

#

#

#

#

#

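### Baseline TFI is self-reported after the open-label allocation is planned to be disclosed, so an arm-differential shift would enter the change-score version of the primary test

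*Protocol*

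**What the plan says.** Four places in the protocol set the order of events.

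- Section 7.6: after randomisation, a member of the central team will "inform the participant during their eligibility call or directly call the participant to inform them of their randomisation allocation", with an email confirmation to follow.
- Section 7.7: "Once randomisation has been confirmed and prior to starting the intervention, participants will report baseline measurements in their survey". The window is Day 1 plus up to 7 days, and the survey includes TFI, EQ-5D-5L and HUI3.
- Appendix 1 (flow chart): randomisation falls in the enrolment box. Next comes a box for notifying sponsor, participant and GP ("Details of randomised participants shared and enrolment confirmed"). Baseline is collected in the box after that.
- Appendix 2 (schedule): randomisation is at Day 0 and baseline at Day 1 with 7 days' allowance. No TFI is scheduled earlier.

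Section 7.8 adds: "Following baseline data collection the participant will be granted access to either the trial intervention or control intervention". Sections 2 and 5.1 describe the trial as open-label.

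The primary outcome is defined in two ways. Section 10.1 says "The primary outcome will be reduction in total TFI score at the 6 month point in the ITT population" and compares the mean difference in reduction with the margin. The synopsis and the Section 4 table give the total TFI score at 6 months, with no reference to change.

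**The concern.** A baseline is safe to subtract, or to adjust for, because it is fixed before anyone knows the allocation. Here it is a subjective questionnaire answered by someone who, on the planned order, already knows whether they will use an app or see a therapist. Relief or disappointment can move the answers. If it moves them by different amounts in the two arms, the difference is carried into every quantity computed from baseline.

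Three things are at stake:

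- **Primary comparison.** Under Section 10.1 the baseline is half of each change score.
- **Economic evaluation.** Section 11.1 starts the QALY area under the curve at the baseline utility and allows regression adjustment for baseline imbalance.
- **Completeness.** Someone who loses interest on hearing their arm is already randomised. They may have no baseline, so the change score has to be imputed. Such losses can differ by arm.

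**Working it through.** **Inputs.** From Section 10.2: margin 13 points, SD 31, one-sided α 2.5% (matching the 95% interval in Section 10.1), 90 per group. The section does not say whether SD 31 refers to the score or to change; I assume change. The size of any baseline shift is not in the protocol and is also assumed.

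**The plan's own figure.** n per group = 2 × 31² × (z₁₋α + z₁₋β)² / 13².

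- At 90% power: 1922 × (1.960 + 1.282)² / 169 ≈ 119.5, so 120.
- At 80% power: 1922 × (1.960 + 0.842)² / 169 ≈ 89.3, so 90.

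The stated 90 per group therefore corresponds to about 80% power, not the stated 90%. That is a separate matter, but it sets the starting power below.

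**Standard error.** SE = 31 × √(2/90) = 4.62.

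**How a shift enters.** Let d be the control-arm reduction minus the app-arm reduction, so positive values mean the app does worse. Non-inferiority is concluded if d + 1.96 × SE < 13. If app participants rate themselves b points worse at baseline, relative to controls, purely because they know their arm, the app-arm reduction grows by b and d falls by b. With true difference δ:

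P(conclude non-inferiority) = Φ((13 − δ + b)/SE − 1.96)

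- False non-inferiority (δ = 13): Φ(b/4.62 − 1.96).
- Power when the shift goes against the app (δ = 0, shift −b): Φ((13 − b)/4.62 − 1.96).

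| Assumed differential shift b (points) | False non-inferiority, shift towards app | Power, shift against app |
|---|---|---|
| 0 | 2.5% | 80.3% |
| 1 | 4.1% | 73.8% |
| 2 | 6.3% | 66.3% |
| 3 | 9.5% | 58.1% |
| 5 | 19.0% | 41.0% |

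For b = 3: Φ(0.649 − 1.960) = Φ(−1.311) = 9.5%, and Φ(10/4.62 − 1.960) = Φ(0.204) = 58.1%. Three points is 3/13 = 23% of the margin, 3/31 = 0.10 SD, and 3/250 = 1.2% of the scale.

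**If baseline TFI were a covariate.** The bias becomes slope × b. With an assumed slope of 0.5 to 0.7, a 3-point shift leaves 1.5 to 2.1 points, and false non-inferiority is 5.1% to 6.6% with SE held at 4.62. An adjusted model should have a smaller SE, which would push those probabilities up somewhat.

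**If the 6-month totals are compared without baseline.** The shift does not enter, and the bias from this source is zero.

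**The case against.** Several counter-arguments have force.

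- **The definition matters.** The synopsis and Section 4 name the 6-month total, which needs no baseline. A reader might infer that the primary result is exposed whichever definition is used. It is not: only the Section 10.1 change score carries the shift in full.
- **Baseline TFI is not a named covariate.** Section 10.1 lists the stratification variables and other potential confounders. The attenuated figures apply only if baseline TFI is among the latter.
- **Treatment cannot have touched the baseline.** Section 7.8 grants access only after baseline collection, which also gives participants a reason to complete it. The issue is knowledge of the arm alone.
- **Disappointment may be limited.** Both arms receive active therapy, and controls have rapid access and are offered the app at 12 months (Section 8.2). This makes a large shift less likely but does not show that it is zero.
- **The shifts are assumptions.** An average of 3 to 5 points across all participants is 23% to 38% of the margin. A reader might infer a bias in the app's favour; nothing in the protocol supports a direction or a size.
- **Disclosure before the survey is inferred for each participant.** No sentence says that everyone knows their arm before answering. It is nevertheless the planned order, and nothing withholds the allocation until the survey is done.
- **Missing baselines have safeguards.** Section 7.1 provides reminders and Section 10.4 multiple imputation. Someone who leaves on hearing their arm would probably also lack a 6-month score, which reordering does not recover, although an observed baseline would help the imputation.
- **The 6-month TFI is also unblinded self-report.** That is true, and this change leaves it untouched. That exposure comes with the open-label design, whereas this one is avoidable.

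**Conclusion.** The point holds as an avoidable risk of bias, not as a demonstrated bias. On the planned order, the arm is disclosed before the only pre-treatment TFI is recorded. Under the Section 10.1 definition, an arm-differential shift passes point for point into the non-inferiority estimate. It would be attenuated but not removed by baseline adjustment, and absent from an unadjusted 6-month comparison. Baseline utilities carry the same exposure into the QALYs.

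The size is illustrative only. A 3-point differential shift takes false non-inferiority from 2.5% to 9.5% in one direction, or power from about 80% to 58% in the other. This rests on SD 31 applying to change, 90 analysed per arm, and a shift whose size and sign the protocol does not give. No later analysis could verify that the shift was zero, which is the reason to remove it by design.

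**What to change.** 1. Amend Sections 7.6 and 7.7 and Appendices 1 and 2 so that TFI, EQ-5D-5L, HUI3 and the tinnitus background survey are completed after consent and eligibility and before randomisation. At the least, they should be completed before the allocation is disclosed. Require a completed baseline TFI before a participant can be randomised.
2. Reconcile the primary outcome in the synopsis and Section 4 (6-month total) with Section 10.1 (reduction), so that it is clear whether baseline enters the primary test.
3. For participants already randomised under the current order, add a sensitivity analysis that compares 6-month TFI between arms without using the baseline value and keeps all of them. Excluding people with post-allocation baselines is not workable, because under the current order that is everyone.

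The cost is modest and the sample size is unaffected. Consent, eligibility and the hearing test already take place remotely before randomisation (Sections 7.3 to 7.5). The additions are a somewhat longer pre-randomisation step, or a short wait for a survey link to be completed, some baselines from people who are then not randomised, and a protocol amendment, which may count as substantial under Section 17.3.
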